#### Interim analysis.

Interim analyses will be part of a yearly steering committee meeting or at every 100 participants recruited, whichever comes first. The trial will implement a modified alpha spending function to guide decisions on early stopping. Initially, at 100 participants, a non-inferiority margin of 0.35 will be applied. This threshold will decrease by 0.05 at each subsequent interim analysis, reaching a final margin of 0.10 after 500 participants have been recruited. If the observed difference exceeds the non-inferiority margin at an interim analysis, the trial will be stopped for inferiority.

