### Timeline

Participant recruitment is expected to commence in early 2025. Recruitment and data collection are expected to be completed within two years. Results are expected shortly after, placing the trial completion date in late 2027 or early 2028. It is expected that an average of 3–6 swabs will be obtained per week across collection sites. Some situations, such as outbreaks or mass gathering events, will allow for greater numbers of swabs to be collected in a small timeframe. After participants return the test samples, they will receive a follow-up phone call. Results of the bulk faeces test will be returned to the patient by the clinician that requested the test.

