#### Decision rules.

Stopping for Safety: Predefined criteria for stopping the trial if a significant safety concern are identified; for instance, if the incidence of severe adverse events is above what is expected.Stopping for Efficacy: Criteria for stopping the trial early if rectal swabs show clear and overwhelming evidence of inferiority, based on predefined statistical thresholds and thus it is futile to continue. A cutoff of 0.35 difference in accuracy for inferiority with an alpha of 0.05 at interim analyses will be used to support decisions on continuing, modifying, or stopping the trial. As this is a diagnostic test trial, the decision to stop the trial must be multifactorial in nature and made by the Trial Steering Committee.

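### The interim inferiority schedule does not reach its own end point (0.35 falling by 0.05 every 100 gives 0.15 at 500, not 0.10) and conflicts with the single 0.35 cutoff in the decision rules

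*Protocol article*

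**What the plan says.** Two sections of the protocol article govern early stopping for inferiority.

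**Statistical methods, Interim analysis.** On timing: "Interim analyses will be part of a yearly steering committee meeting or at every 100 participants recruited, whichever comes first". On the threshold: "Initially, at 100 participants, a non-inferiority margin of 0.35 will be applied", and then "This threshold will decrease by 0.05 at each subsequent interim analysis, reaching a final margin of 0.10 after 500 participants have been recruited". On the consequence: "If the observed difference exceeds the non-inferiority margin at an interim analysis, the trial will be stopped for inferiority". The section calls this scheme a modified alpha spending function.

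**Oversight and monitoring, Decision rules.** Under stopping for efficacy: "A cutoff of 0.35 difference in accuracy for inferiority with an alpha of 0.05 at interim analyses will be used to support decisions". No decrease is mentioned. The section adds that "the decision to stop the trial must be multifactorial in nature and made by the Trial Steering Committee".

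The Timeline section gives the forecast that decides how many looks there will be: "It is expected that an average of 3–6 swabs will be obtained per week across collection sites", with recruitment expected to finish within two years. The sample size section fixes no single target. It says fewer than 600 samples will suffice and considers funding for as few as 40.

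**The concern.** A stopping boundary has to give one answer for a given set of data. Here the start, the step and the end point of the schedule do not agree when looks fall every 100 participants. A second section then gives a different cutoff, a different kind of evidence and a different force.

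The rule governs whether the trial continues on its primary comparison. If the Trial Steering Committee has to choose between the two versions after seeing interim data, the rule is no longer prespecified. The threshold is also counted down by looks, so the standard in force at a given sample size can depend on how fast people were recruited.

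**Working it through.** **1. The schedule against its stated end point**

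Inputs, all from the Interim analysis section: start 0.35 at 100 participants; step 0.05 per later look; a look at every 100; stated end point 0.10 after 500.

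Formula: threshold at look k = 0.35 − 0.05 × (k − 1), with look k at 100k participants.

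| Participants | Look | Threshold |
|---|---|---|
| 100 | 1 | 0.35 |
| 200 | 2 | 0.30 |
| 300 | 3 | 0.25 |
| 400 | 4 | 0.20 |
| 500 | 5 | 0.15 |
| 600 | 6 | 0.10 |

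The stated 0.10 at 500 is not reproduced. Five looks contain four steps, and 0.35 − 4 × 0.05 = 0.15. Any one of three changes would close the gap:
- a step of (0.35 − 0.10) / 4 = 0.0625;
- a start of 0.10 + 4 × 0.05 = 0.30;
- an end point at 600.

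The document does not show which figure is the slip.

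**2. Dependence on accrual and calendar**

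Inputs: 3 to 6 swabs per week (Timeline), each counted as one participant; two years taken as 104 weeks; steady accrual assumed. Participants = rate × 104, so 312 to 624. The timing sentence can be read in two ways: only the 100-participant looks occur, or yearly looks at weeks 52 and 104 are added and each lowers the threshold.

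| Per week | Participants | Count looks only: looks, last threshold | Count plus yearly looks: looks, last threshold |
|---|---|---|---|
| 3 | 312 | 3, 0.25 | 5, 0.15 |
| 4.5 | 468 | 4, 0.20 | 6, 0.10 |
| 5 | 520 | 5, 0.15 | 7, 0.05 |
| 6 | 624 | 6, 0.10 | 8, 0.00 |

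In the last column, 0.05 and 0.00 follow from the step alone. If 0.10 is meant as a floor, they would be 0.10.

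If the yearly clock restarts after each look, the yearly trigger never comes first at the forecast rates: 100 participants take 100/3 = 33 weeks at the slowest rate, which is under 52. The count-only column then applies.

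Reaching 500 within 104 weeks needs 500/104 = 4.8 per week. No final margin is stated for a trial that ends below 500, and at 40 participants no count-based threshold has yet been set.

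**3. The two sections side by side**

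| | Interim analysis | Decision rules |
|---|---|---|
| Cutoff | Falls at each look | 0.35 at interim analyses |
| Evidence | Observed difference | Alpha of 0.05 |
| Force | Trial is stopped | Supports a multifactorial committee decision |

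Take an observed difference of 0.25 at 400 participants. Under the schedule the threshold is 0.20, or 0.15 if one yearly look has already occurred, so the trial stops. Under the Decision rules, 0.25 is below 0.35 and the cutoff is not reached. The conflict holds on either reading of the timing sentence.

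**The case against.** The schedule can be read so that it closes. If the end point means the look following 500, that is the look at 600, and 0.10 is exact. It also closes if one yearly look falls before 500: at 5 per week, looks at 100, 200, 260, 300, 400 and 500 make six, and 0.35 − 5 × 0.05 = 0.10. The sample size section's figure of fewer than 600 is a statement about sufficiency, not a recruitment cap, so it does not exclude the first reading. This stands as far as it goes: the arithmetic fault is one step and may be ambiguity rather than error. But a stopping boundary should not need such a choice, and the conflict with the Decision rules remains either way.

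The difference in force is also partly softened. The Interim analysis section says the scheme is there to guide early stopping, and the oversight section gives stop-early decisions to the committee's oversight. Only the sentence that makes stopping automatic conflicts.

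Four stronger readings are tempting and are not supported:
- A reader might infer that a swab could be called non-inferior at 0.35 or 0.25 if recruitment is slow. Both sections attach a consequence only to inferiority, the primary analysis is estimation with 95% confidence intervals, and 0.10 is called the final margin. A futility threshold that is lenient early and tightens later is a recognised design choice.
- A reader might infer that three cutoffs apply at 500. The text states 0.10 and 0.35; 0.15 is derived.
- A reader might count discordant pairs to compare the two rules at 100 participants. The document does not define the difference in accuracy that way and does not say whether the alpha is one-sided.
- A reader might conclude that no alpha is spent. Allocation per look may sit in an analysis plan that is not shown. What can be said is that the scheme described here is a changing margin, which the label does not describe.

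**Conclusion.** The point holds as a fault in what is written, not as missing detail. With looks every 100, the schedule gives 0.15 at 500 against a stated 0.10, one step of 0.05 apart, and first reaches 0.10 at 600. The Interim analysis and Decision rules sections state interim rules that cannot both be followed. At 400 participants the two cutoffs are 0.20 and 0.35, so any observed difference above 0.20 and below 0.35 stops the trial under one and does not reach the cutoff of the other.

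The dependence on accrual is real, but its size rests on how the timing sentence is read and on steady recruitment. The threshold at the last look runs from 0.25 to 0.10 across the forecast on count looks alone, and takes different values if yearly looks also count. An unseen analysis plan could follow one section only by departing from the other, so the article's own text needs reconciling before the first interim look.

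**What to change.** State one interim inferiority rule and use the same wording in both sections.

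1. Tabulate the thresholds by number of participants, not by look count, and correct the start, step or end point so that the three agree. Say which tabulated value applies at a yearly look that falls between counts or before 100.
2. State one criterion. Preferably, the confidence bound for the difference must lie beyond the threshold, rather than the point estimate alone, with the level and sidedness given.
3. State once whether the rule binds or is advisory to the Trial Steering Committee.
4. Fix the final margin independently of how many are recruited: the protocol's own 0.10, or another value that the sponsor justifies.
5. Drop the alpha spending label unless alpha is actually allocated to looks.

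The cost is a change of wording. The one substantive downside is that an inferiority stop based on a confidence bound triggers later than one based on the point estimate. The fix does not require the same margin at every look. It also does not add a final success criterion, which would be a separate design decision needing its own power check.

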#### Objectives of interim analysis.

Recruitment Rates: Assess the rate of recruitment and discuss the barriers and facilitators to successful participant recruitment.Safety Monitoring: Ensure participant safety by identifying any significant adverse events early. Review adverse event reports, including severity, relatedness, and unexpected events. Analyse differences in safety profiles between the rectal swab and bulk faeces groups.Efficacy Assessment: Non-inferiority assessments will be performed to monitor for inferiority of rectal swab PCR in comparison with traditional bulk faeces testing. Evaluate the primary endpoint of difference of accuracy of specimen collection methods, the rate of pathogen detection.Trial Continuation Decision: Provide data to support decisions on continuing, modifying, or stopping the trial.Compliance and Protocol Adherence: Assess the adherence to study protocols, including the proper collection and handling of specimens.

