## Abstract

Obtaining a stool specimen for diagnostic testing of enteric conditions (e.g., gastroenteritis) can be a challenging and unpleasant experience. A person is required to obtain a sample pot from a healthcare location, return home and wait until they have a bowel motion, and then deal with the challenges of returning the sample to the clinic or pathology centre. This trial aims to identify whether the simpler approach of obtaining a rectal swab is effective for diagnosing enteric conditions. Recruitment will take place in a variety of settings, including suspected norovirus clusters, Hepatitis A clusters, in both hospital, and community settings. We will compare paired stool and rectal swab sample polymerase chain reaction (PCR) testing to determine whether rectal swabs are a reliable proxy for faecal sampling. Persons who would normally be provided with a faecal specimen container, will also be provided with a rectal swab for self-collection or clinician-collection (within 24 hours of the bulk faeces collection). We will assess the sensitivity, specificity, positive predictive value, negative predictive value using standard confusion matrix. The gold standard reference will be considered the bulk faeces PCR tests. We hypothesise that rectal swab PCR testing will be equally as effective as bulk faeces PCR testing. If successful, rectal swab PCR testing could be implemented as routine practice with several key benefits. Firstly, it would improve the patient experience by conveniently enabling stool collection at the point of care, which is rarely possible currently. Secondly, it would reduce healthcare costs, and streamline collection processes by eliminating the need for persons to return to a clinic to deliver specimen. Thirdly, the ease of testing will likely increase testing rates and compliance, leading to better diagnoses and more accurate clinical care. The protocol described has the potential to revolutionise daily clinical practice.

**Trial registration**: Australian New Zealand Clinical Trials Registry (ANZCTR): ACTRN12624000095561.

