Studies have long compared rectal swabs vs bulk faeces testing. The results are varied, depending on the year the study was performed. An early study examining 700 specimens tested with MacConkey’s medium in 1940 during a Sonne dysentery outbreak (*Shigella sonnei* sp. outbreak) found that rectal swabbing was far superior to bulk faeces culture to detect an organism [8]. Rectal swabbing became the standard for a period of time This was disputed later in 1954 after a group examined 3,183 index cases looking for a variety of organisms to which they concluded that the *“…626 [bulk faeces] specimens all showed abnormalities which could be demonstrated only by microscopy or simple chemical methods, for which the rectal swab is quite unsuitable”* [9]. Since then, huge changes have occurred to our detection methods (e.g., culture media) and the advent of PCR testing for multiple organisms at once.

More recent studies demonstrate that the differences between rectal swabs and faecal samples is driven by the type of test (bacterial microscopy and culture vs viral PCR). A phase I clinical study for a live oral attenuated *Salmonella* Typhi vaccine strain found that when compared with faecal culture, rectal swabs were 64% sensitive and 90% specific [10]. A recent study on paired samples found that for bacteria, the sensitivity was 86.5% (95% CI 79.5%, 91.8%) when PCR was performed and 61.4% (95% CI 52.4%, 69.9%) when culture for bacteria was performed, indicating better performance for PCR [11].

It has been shown in small studies that rectal swabs are likely accurate. Studies have now shown that during testing for various enteric organisms (viruses and bacteria) in Rwandan children there was no significant difference in detection rate between faeces and rectal swabs for any agent, reflecting that pathogen concentration was far above the limit of detection in the majority of cases [12]. A similar paired sample study focusing on norovirus found a sensitivity of rectal swabs that was greater than 97%, and in one case detected norovirus in the swab, but not in the bulk faeces [13].

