#### Control sample (bulk faeces).

The bulk faeces sample is used as the control sample in this study as this sample type is currently used in routine clinical practice. In this context, bulk faeces PCR testing is considered the gold standard. It is acknowledged that bulk faces PCR testing may be associated with technical or interoperability limitations. To minimise the uncertainty that this could pose on testing results, paired samples that do not produce the same results will be managed internally according to laboratory protocol.

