#### Primary outcomes.

We will assess the sensitivity, specificity, positive and negative predictive value, and positive and negative agreement value, using 2x2 tables. The gold standard will be bulk faeces PCR testing. Sensitivity is the proportion of individuals with the disease who test positive with rectal swabs. We will assess the cycle threshold (CT) values using general linear models if the relationship is linear as expected and estimate the receiver operating curves and areas under the curve to assess for the potential to need differential CT value cutoffs. All results will be reported using 95% confidence intervals.

The R statistical suite will be used for all analyses and data visualisation. All estimates will be presented with 95% confidence intervals (CI). P-values <0.05 are deemed significant, and p-values <0.1 are considered trends.

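### The inferiority margin sits on a difference in accuracy that equals total swab–bulk discordance, so it ignores direction and can label an equal or better swab inferior

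*Protocol article*

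**What the plan says.** All references are to the protocol article.

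- *Abstract*, the hypothesis: "We hypothesise that rectal swab PCR testing will be equally as effective as bulk faeces PCR testing".
- *Primary outcomes*, the reference: "The gold standard will be bulk faeces PCR testing". *Control sample (bulk faeces)* nevertheless concedes a weakness: "It is acknowledged that bulk faces PCR testing may be associated with technical or interoperability limitations".
- *Interim analysis*, the margins: "Initially, at 100 participants, a non-inferiority margin of 0.35 will be applied". They fall by 0.05 per analysis, "reaching a final margin of 0.10 after 500 participants have been recruited". The consequence is: "If the observed difference exceeds the non-inferiority margin at an interim analysis, the trial will be stopped for inferiority". This section does not name the scale of the difference.
- *Decision rules* names it. The cutoff there is a 0.35 difference in accuracy with alpha 0.05. The same section makes stopping a multifactorial decision of the Trial Steering Committee.
- *Objectives of interim analysis* sets the endpoint: "Evaluate the primary endpoint of difference of accuracy of specimen collection methods, the rate of pathogen detection".
- *Introduction* describes a paired norovirus study that "in one case detected norovirus in the swab, but not in the bulk faeces". *Discussion* foresees discordance in both directions and sends such pairs for additional testing, without saying whether that result enters the analysis.

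**The concern.** A claim that two sampling methods are equally effective is about net detection: does one find organisms less often than the other? A margin on accuracy against bulk answers another question, because bulk cannot be wrong by definition and every swab-only positive counts as a swab error. A swab that finds more organisms moves towards the inferiority boundary, just as a swab that misses them does. The committee would then receive a statistic labelled inferiority that cannot distinguish a worse swab from a better one.

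**Working it through.** **Inputs.** From the protocol: bulk as reference; margins from 0.35 to 0.10; 30% of samples positive and an expected swab sensitivity of 95% (*Sample size calculation*). Assumed: the share of infections that bulk PCR finds, which the protocol does not give; other swab values; and 50% infected for an enriched sample. Enrichment is plausible because *Sample size calculation* (text after Fig 2) and *Recruitment* describe targeting people with high pre-test probability.

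**Step 1: margin schedule.** Steps of 0.05 from 0.35 at n = 100 give 0.30, 0.25, 0.20, 0.15 and 0.10 at n = 200, 300, 400, 500 and 600. So 0.10 is reached at the 600 look, although the text can also be read as applying it at 500. Both readings are shown below.

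**Step 2: algebra.** Let a = both positive, b = swab-only, c = bulk-only, d = both negative, n = a + b + c + d.

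- Accuracy of bulk against itself = 1. Accuracy of swab = (a + d)/n = 1 − (b + c)/n.
- Accuracy difference = (b + c)/n, which is never negative.
- Detection-rate difference = (a + c)/n − (a + b)/n = (c − b)/n.

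The two agree only when b = 0.

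**Step 3: three tables at n = 500.**

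| b (swab-only) | c (bulk-only) | (b + c)/n | (c − b)/n | Swab is |
|---|---|---|---|---|
| 30 | 30 | 0.12 | 0.00 | equal |
| 60 | 0 | 0.12 | −0.12 | better |
| 0 | 60 | 0.12 | 0.12 | worse |

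All three exceed 0.10 on the accuracy scale; only the third does on the detection scale. Steps 2 and 3 need no assumption about test performance.

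**Step 4: how often it would matter.** With proportion infected p, swab finding share s, bulk finding share t, independent misses and no false positives: b/n = p·s·(1 − t), c/n = p·t·(1 − s), and D is their sum. The last two columns are binomial tail probabilities that observed discordance exceeds 0.10.

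| p | s | t | b/n | c/n | D | (c − b)/n | n = 600 | n = 500 |
|---|---|---|---|---|---|---|---|---|
| 0.30 | 0.95 | 0.95 | 0.014 | 0.014 | 0.029 | 0 | about 0 | about 0 |
| 0.30 | 0.90 | 0.90 | 0.027 | 0.027 | 0.054 | 0 | about 0 | about 0 |
| 0.30 | 0.80 | 0.80 | 0.048 | 0.048 | 0.096 | 0 | 34% | 35% |
| 0.30 | 0.95 | 0.80 | 0.057 | 0.012 | 0.069 | −0.045 | 0.2% | 0.4% |
| 0.50 | 0.90 | 0.90 | 0.045 | 0.045 | 0.090 | 0 | 18% | 19% |
| 0.50 | 0.95 | 0.80 | 0.095 | 0.020 | 0.115 | −0.075 | 86% | 84% |

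On the Step 1 schedule, the looks before 600 add almost nothing. In the last row the 0.15 margin at n = 500 is crossed in 0.7% of trials. With a flat 0.35 cutoff the chance is about 0 in every row. With correlated misses (latent correlation 0.5), the 86% falls to 33% and the 34% to about 0.

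**Step 5: the same cases on the detection scale, n = 600.** The standard error of (c − b)/n is √{[D − ((c − b)/n)²]/n}.

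- Both at 80%, p = 0.30: √(0.096/600) = 0.0126. The margin lies 0.10/0.0126 = 7.9 standard errors above the true value of 0.
- Swab 95%, bulk 80%, p = 0.50: √[(0.115 − 0.0056)/600] = 0.0135. The margin lies (0.10 + 0.075)/0.0135 = 13 standard errors above the true value.

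In both cases the false-stop chance is about 0. In the last case the swab's specificity against bulk would read 1 − 0.095/(1 − 0.50 × 0.80) = 0.84 despite no false positives. Bulk-referenced measures are therefore better labelled as agreement.

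**The case against.** **Routine care is a legitimate reference, and the trial also asks whether the swab is a reliable proxy.** This stands in part. Thirty misses offset by thirty swab-only positives is not interchangeability, so total discordance deserves reporting. It is not evidence of inferiority, however, and the margin is labelled as a test of inferiority.

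**The rate of pathogen detection may be the quantity intended.** If so, the problem disappears. But *Objectives of interim analysis* presents it as the same thing as accuracy, and *Decision rules* fixes the cutoff on accuracy.

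**Safeguards exist.** The committee decision softens the automatic stop in *Interim analysis*, and a flat 0.35 cutoff would remove the risk in every scenario above. Both reduce the consequence, but the committee would still receive a direction-blind statistic. Additional testing of discordant pairs could help, but no analytic role is given to it. Positive and negative agreement are primary outcomes, but they do not carry the margin.

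**Frequent independent misses by bulk PCR are not established.** This stands. The *Introduction* offers one swab-only norovirus detection, and also a paired study with no significant difference because concentrations mostly lay far above the detection limit. A reader might take the 1940 study favouring swabs as evidence that bulk stool misses infections. It used culture, was later disputed, and says nothing about bulk PCR.

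**A reader might infer that the trial cannot confirm its hypothesis.** The protocol does not support that. It sets no success threshold for sensitivity or for an upper confidence limit; its stated rule only stops for inferiority.

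**Conclusion.** The endpoint is misdefined: with bulk as the reference, the accuracy difference is total discordance, and the protocol equates it with a detection rate from which it differs whenever there is a swab-only positive. That conclusion is algebraic. The rule as written therefore tests neither inferiority nor equal effectiveness.

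The practical size is limited. A false inferiority signal needs the late margins (0.15 to 0.10) together with an enriched sample or a clearly imperfect bulk PCR. A reader might infer that the trial is likely to be stopped because the swab is better. The documents do not support that: at the protocol's 30% positive, with the swab at 95% and bulk at 80%, the chance is about 0.2%. The 86% figure needs 50% infected and bulk missing one infection in five, and arises almost entirely at the 0.10 margin. All these probabilities rest on assumed detection shares, independent misses and no false positives. The change is worth making because the rule is stated in the protocol and correcting it is cheap.

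**What to change.** In *Interim analysis*, *Objectives of interim analysis* and *Decision rules*:

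- Apply the margin to the paired detection difference, (bulk-only − swab-only)/n, on first-run results, with a paired 95% confidence interval (e.g. Tango or Newcombe). Stop naming accuracy and detection rate as one endpoint.
- Keep n as the denominator so that the stated margins keep their scale. Dividing by pairs positive on either sample would put the same margins on a different scale without justification.
- Report swab-only and bulk-only counts separately.
- Keep sensitivity, specificity and total discordance against bulk beside the paired difference, labelled as agreement with bulk, because they bear on interchangeability.
- Reconcile the falling margins in *Interim analysis* with the single 0.35 cutoff in *Decision rules*, and state the look at which 0.10 first applies.

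The cost is protocol wording and one extra estimate from the same 2×2 table, with no new samples. The downside is that false-positive swabs can offset misses in the net difference, so the bulk-referenced specificity and sensitivity must always be shown with it.
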